**Protocol #: 16-0510**

**Project Title:** Values and Hypertension Study

**Principal Investigator:** [name]

**Version Date:** 12-05-20

**Hypotheses and Specific Aims:** The objective of the study is to reduce the effects of stereotype threat on the adherence of African American patients with hypertension. We hypothesize that stereotype threat impairs communication between minority patients and their providers resulting in decreased patient engagement and lower rates of adherence with antihypertensive medication. We propose an innovative approach using values affirmation to overcome the stereotype threat to increase patient activation, improve adherence and thereby reduce disparities in hypertension outcomes. Our proposal is based upon our pilot study demonstrating a brief values affirmation exercise done immediately before a clinic visit resulted in improved communication between African American patients and providers during the visit and suggested improved medication adherence 6-months after the visit. We propose to advance our prior work and fill gaps in the evidence by conducting a randomized controlled trial comparing a values affirmation exercise to a control exercise among 1,130 patients with hypertension from three health systems. The primary outcome is 6-month adherence to antihypertensive therapies with the secondary outcomes of blood pressure, time under blood pressure control, and treatment intensification. We will also explore possible mechanisms of the intervention effect and formally examine the potential for widespread dissemination.

The specific aims are to:

**Aim 1.** Compare the effects of the values-affirmation exercise to a control condition on antihypertensive medication adherence in African American patients with uncontrolled hypertension across three clinical settings.

**H1:** Those performing the values-affirmation exercise will have increased antihypertensive medication adherence over the ensuing 6-months compared to the control condition

**H2:** The effect of values affirmation will be partially moderated by patient factors (prior experience with discrimination), and provider factors (implicit racial bias, past disparities training, self-efficacy for caring for minority patients), and mediated by the theory-driven factors of patient activation, attitudes, perceived social norms, perceived behavioral control and anticipated emotion regarding management of blood pressure.

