**Table 1: Patient survey contents**

| Pre-visit Survey              | Post-visit survey               | 3- and 6-month surveys        |
|-------------------------------|---------------------------------|-------------------------------|
| Prior discrimination          | Patient Activation Measure      | Patient Activation Measure    |
| Voils adherence questionnaire | Attitudes Survey                | Attitudes Survey              |
|                               | Patient impression of the visit | Voils adherence questionnaire |

**Prior experience of discrimination.** We will treat perceived discrimination as a potential modifier of the effect of the intervention on adherence. We will use a 4-item questionnaire about prior experience of discrimination modified from prior scales measuring lifetime discrimination related to healthcare. Responses are on a 5-point Likert scale ranging from "never" to "all of the time". (see Prior Discrimination Survey-new version)

**Patient activation.** We will also assess the effect of the intervention on patient activation, our theoretical mediator of the effect of values-affirmation on engaging in hypertension care. (Figure 1) We will use a low-literacy version of the 13-item instrument developed by Hibbard, the Patient Activation Measure (PAM). Increases in the PAM are associated with increase self-management behavior including adherence. Patient activation measured with the PAM is lower for African Americans than it is for whites, and is therefore hypothesized to be a contributing factor to racial health disparities. Few interventions have been shown to be effective for increasing patient activation. Each questions is answered on a 4-point Likert scale.

We will treat the PAM score as a potential mediator of the effect of the interventions on adherence and measure this construct after the index visit and at 3- and 6-months to determine maintenance of effect.

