#### **F. Data Analysis Plan:**

**Sample size estimation.** For our primary analysis, we assume a three-level model, with patients nested within providers and providers nested within clinics. Assuming comparable variation in adherence and  $\alpha=0.05$ , a sample size of 960 subjects (240 each cell in values affirmation, or control; 480 African American, 480 white) will be required to detect an effect size of 0.26 difference in adherence between any two cells with a power of 80%. Based on the pilot study results, a 0.26 effect size is approximately a 4.7% absolute difference in adherence scores. Since randomization is at the patient level, the intraclass correlation coefficient for patients nested within clinicians will

have a negligible effect on power. We conservatively estimate an attrition rate (neither having a med refill within the system nor returning for follow up) over all sites of 15%. We therefore will enroll an additional 170 patients to compensate for this attrition, for a final sample size of 1,130. We will cap enrollment at 450 subjects per site to ensure generalizability of results.

For moderation hypotheses, the primary contrast of interest is the adherence difference between African Americans with high and low past experiences of discrimination (dichotomized scores for ease of interpretation) who receive the intervention. Using a median split on the discrimination scores, the sample size for this comparison would be 120 in each subgroup. This sample size will provide >80% power to detect a 0.37 SD difference in adherence. For the patient activation mediation analyses, a sample size of 480 (e.g. African Americans only) will provide >80% power to detect a 0.13 partial correlation between change in the patient activation and change in adherence, adjusting for other variables in the model; a sample size of 960 will provide >80% power to detect a .10 partial correlation. Parchman et al report a standardized regression coefficient of 0.16 between patient activation and the Morisky medication adherence scale. While our proposed analytic approaches differ, this gives some indication of the anticipated strength of the relationship.

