The primary outcome variable (adherence measured by pharmacy refills) is continuous; in the event that normality assumptions are not met we will use transformations to normalize distributions. For the primary comparisons, we will employ intent-to-treat analyses, although we expect few or none of the randomized patients to not complete an exercise. We will examine overall values affirmation effectiveness between the racial groups. We will next create models with adherence as the dependent variable including the potential moderator variable (prior experience of discrimination) then including the potential mediator variables (patient activation, attitude, social norms, perceived behavioral control, and anticipated emotion). Finally, we will explore whether the collected provider variables (racial bias, past cultural competency training, self-efficacy and racial mix of clinical site) moderate the relationships. We will also include patient gender and provider race as a possible moderating variables. We will use general (or generalized, for dichotomous outcomes) linear mixed models, examining alternative structures for the variance-covariance matrix for the level 1 model by comparing goodness of fit for the different models as well as model fitting diagnostics to assess for influential points, outliers, overdispersion and heteroscedasticity. We will employ methods that utilize all available data, assuming ignorable missingness.

In secondary analysis using the self-reported adherence measures, we will dichotomize the groups into non-adherent (score  $\geq 2$  on any "extent" item) and adherent. We will also compare the pill count measure of adherence to the pharmacy fill estimates of adherence for validation. For blood pressure, the secondary outcome, we will compare the index and follow-up visits using mixed effects repeated measures models with a patient random effect. All hypothesis tests will be two-sided with  $\alpha=.05$ . Statistical analysis will use SAS 9.4.

**Statistical Model for Primary Outcomes.** The structure of the data is hierarchical (patients nested within providers) and longitudinal (repeated measures on patients over time). Baseline (time 0) is defined as the adherence rate for the 12-months prior to the index visit.

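### The contrast named for discrimination as a moderator uses the intervention arm only, so neither it nor its >80% power at 0.37 SD addresses the moderation part of H2

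*Protocol*

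**What the plan says.** H2, under Aim 1 in the Hypotheses and Specific Aims, reads: "The effect of values affirmation will be partially moderated by patient factors (prior experience with discrimination", followed by provider factors and mediators. The description of the discrimination questionnaire in section IV.C, under Table 1, gives the score the same role: "We will treat perceived discrimination as a potential modifier of the effect of the intervention on adherence".

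Section F (Data Analysis Plan, Sample size estimation) sets the trial at "a sample size of 960 subjects (240 each cell in values affirmation, or control; 480 African American, 480 white". For the moderation hypotheses it then states that "the primary contrast of interest is the adherence difference between African Americans with high and low past experiences of discrimination", with the qualification "dichotomized scores for ease of interpretation) who receive the intervention". It continues: "Using a median split on the discrimination scores, the sample size for this comparison would be 120 in each subgroup", and "This sample size will provide >80% power to detect a 0.37 SD difference in adherence".

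The Statistical Analysis text of section F says that the adherence models will include prior discrimination as a potential moderator. It names no product term between arm and discrimination. The Level 2 equations contain an intervention-by-race product and leave other patient covariates unshown. Section F also states: "All hypothesis tests will be two-sided", at a level of 0.05.

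**The concern.** Moderation is a statement about the difference between arms: is intervention minus control larger in patients with more past discrimination than in those with less? The named contrast has no control patients in it. The wording, the subgroup size (half of one 240-patient cell) and the power figure all agree on this, so it is not a slip of phrasing.

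Inside one arm, high against low discrimination compares patients on a trait they brought to the trial. Randomisation does not protect that comparison. If adherence over follow-up moves differently by discrimination for reasons unrelated to the exercise, the contrast picks this up and it can be read as moderation. An offsetting trend could equally hide real moderation. Only the control arm shows what the trajectories would have been.

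At stake are the inference on the discrimination part of H2 and the trust a reader can place in its power. The protocol gives no power for an interaction with discrimination, so the >80% figure stands in for it.

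**Working it through.** **Inputs (section F).** Evaluable patients: 960, which is 1,130 enrolled less the 170 added for attrition, so no further reduction applies. African American patients: 480, with 240 per arm. A median split gives 120 per arm-by-discrimination cell (assuming the split falls evenly in both arms). Two-sided level 0.05, critical value 1.96. Stated effect 0.37 SD. The protocol equates 0.26 SD with 4.7 percentage points, so the SD is about 4.7 / 0.26 = 18.1 points.

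**1. The plan's own figure.** High against low within the intervention arm:
- SE = sqrt(2/120) = 0.129 SD.
- Power at 0.37 SD = Φ(0.37/0.129 − 1.96) = 0.818 (0.814 with the noncentral t).
- Detectable at 80% power = (1.96 + 0.842) × 0.129 = 0.36 SD.

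The claim of more than 80% at 0.37 SD reproduces.

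**2. The contrast that H2 describes.** (Intervention − control among high) − (intervention − control among low), four cells of 120:
- SE = sqrt(4/120) = 0.183 SD. The variance is twice that in step 1.
- Power at 0.37 SD = Φ(0.37/0.183 − 1.96) = 0.527 (0.525 with the noncentral t).
- Detectable at 80% power = 2.802 × 0.183 = 0.51 SD, about 0.511 × 18.1 = 9.2 points. The stated 0.37 SD is about 6.7 points.
- Cell size for 80% power at 0.37 SD = 4 × (2.802/0.37)² = 229.3, so 230 per cell, or 920 evaluable African American patients against 480 planned.

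**3. Use of baseline adherence.** Step 2 takes the SD of the outcome as analysed. If 0.37 SD is read in raw-adherence units, the answer depends on the correlation r between baseline and follow-up adherence, which the protocol does not give. The residual SD is multiplied by sqrt(1 − r²) with baseline adjustment and by sqrt(2(1 − r)) with change scores. The values of r below are assumptions.

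| Assumed r | Adjusted: power at 0.37 | Adjusted: detectable at 80% | Change: power at 0.37 | Change: detectable at 80% |
|---|---|---|---|---|
| 0.3 | 57% | 0.49 SD | 40% | 0.61 SD |
| 0.5 | 65% | 0.44 SD | 53% | 0.51 SD |
| 0.7 | 81% | 0.37 SD | 74% | 0.40 SD |

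The same multiplier applies to the one-arm contrast. On any common scale, the interaction's detectable effect is therefore sqrt(2) = 1.41 times as large.

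**4. What the one-arm contrast picks up without moderation.** Suppose the analysed outcome differs by discrimination equally in both arms, by g SD, so that there is no moderation. The one-arm test then rejects about 12% of the time at g = 0.10, 34% at 0.20 and 82% at 0.37, against a nominal 5%. These values of g are illustrations. With change as the outcome, g has to be a difference in trajectory, and the protocol gives no estimate of one.

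**The case against.** The strongest reply is that the sentence is a power statement and not the analysis. The rest of the protocol treats the question as effect modification: the questionnaire description does so, the RE-AIM effectiveness paragraph asks whether the exercise works similarly across groups, and the mixed model covers both arms and allows linear contrasts. An analysis plan not shown may specify the interaction. This stands in part. Both arms complete the discrimination survey before the visit, so the interaction can be fitted, and it would be wrong to infer that the trial cannot test H2. But section F names the one-arm difference as the primary moderation contrast and ties the power to it, and nothing elsewhere in the section replaces it. An analysis plan with the right term would contradict section F, which would still need correcting.

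A reader might go further and infer that the contrast must be non-zero when the exercise does nothing, because discrimination lowers adherence, and must vanish when the exercise fully buffers the threat. That argument is about levels of adherence. The overall strategy in section IV makes change in adherence the primary outcome, and the Level 2 model carries intervention effects on the slope. A stable link between discrimination and adherence then largely cancels, and full buffering would make the one-arm difference in change non-zero. What survives is the narrower point that trajectories may differ by discrimination among controls too.

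A reader might also take the >80% for an arithmetic error. It is not one. Nor is the gap removed by adjustment for baseline: the interaction reaches about 80% at 0.37 raw SD only with an assumed correlation near 0.7, and adjustment does not bring controls into the contrast.

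The median split is a lesser matter. The protocol gives ease of interpretation as its reason, and the modelling text does not require a split score.

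**Conclusion.** The point holds in limited form. The contrast in section F does not match H2 or the stated role of the discrimination score, and its power figure is right for a different question. Like for like, with a median split, power at 0.37 SD is about 53% instead of about 82%, and the difference between arm effects detectable with 80% power is about 0.51 SD. In raw-adherence SD units the detectable effect runs from about 0.37 (baseline-adjusted, r = 0.7) to about 0.61 (change scores, r = 0.3). That range rests on assumed correlations, equal cells of 120 and a common SD.

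The documents do not show that the one-arm contrast would mislead in a known direction or by a known amount, only that it cannot isolate moderation. The discrimination-moderation part of H2 is affected. H1, H3 and the sample size of 960 evaluable (1,130 enrolled) patients are not. Importance: moderate.

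**What to change.** In section F, Sample size estimation, replace the one-arm contrast with the intervention-by-discrimination interaction on change in adherence (or on follow-up adherence adjusted for baseline), among African American patients of both arms. Name the same term in the Statistical Analysis text.

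Restate the power: with a median split and four cells of 120, 80% power for a difference between arm effects of about 0.51 SD of the analysed outcome, and about 53% at 0.37 SD. Give the assumed baseline-to-follow-up correlation, with the range of about 0.37 to 0.61 raw SD.

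Using the continuous score in the model, with the split kept for display, is a reasonable option. If it is taken, power should be calculated for that model, because 0.51 SD describes the median split only.

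The cost is a paragraph of text and a less favourable stated figure. No additional patients or data are needed.

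### The main moderation contrast cuts the prior-discrimination score at its median for readability alone; if the relationship is roughly linear, keeping the full score would recover about a third of the information

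*Protocol*

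**What the plan says.** In the Data Analysis Plan (section IV.F, Sample size estimation), the protocol takes as its main contrast for moderation a comparison of African American patients by "past experiences of discrimination (dichotomized scores for ease of interpretation) who receive the intervention. Using a median split on the discrimination scores". This gives 120 patients in the high half and 120 in the low half. The power claim follows: "This sample size will provide >80% power to detect a 0.37 SD difference in adherence". The 240 patients come from the cell sizes given earlier in that section: "240 each cell in values affirmation, or control; 480 African American, 480 white".

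The score itself is graded. Under Prior experience of discrimination (section IV.C) it is a four-item questionnaire, and "Responses are on a 5-point Likert scale ranging from" never to all of the time.

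The Statistical Analysis text plans adherence models "including the potential moderator variable (prior experience of discrimination"). It does not say whether the score enters whole or cut, and nothing there withdraws the median split.

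**The concern.** Cutting a graded score at its median treats a patient just above the cut like one who reports discrimination all of the time. No validated cut-point and no expected threshold is cited. The sample median has no fixed meaning in another population, and ties on a short ordinal score may prevent an even 120/120 division.

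The same paragraph of the protocol handles another survey score differently: patient activation is left continuous, and its power is stated as a detectable partial correlation (0.13 with 480 patients, 0.10 with 960).

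What is at stake is H2. It names prior discrimination as the patient-level moderator, and this is the only moderator with a power statement. If the true pattern is a gradient, a split makes it easier to miss.

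**Working it through.** **Inputs from the protocol.** 120 per half, 240 in total; 0.37 SD between halves; "All hypothesis tests will be two-sided with" α = 0.05; 480 African American patients, 240 per arm; a score built from four 5-point items.

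**Inputs assumed, because the protocol does not give them.** The score's distribution (normal as base case; uniform, exponential and simulated four-item scores as the range), and a linear relation between the score and adherence, or between the score and the intervention effect.

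**1. The protocol's figure.** Standard error √(2/120) = 0.1291. Then 0.37/0.1291 = 2.866, less 1.960 = 0.906, giving 81.8% (81.4% with the noncentral t). The stated figure of more than 80% reproduces. The difference detectable at exactly 80% is 2.802 × 0.1291 = 0.362 SD.

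**2. The same gradient on the full score, within the intervention arm.** For a normal score, a median split separates the two halves' mean scores by 2√(2/π) = 1.596 SD. So 0.37 SD between halves corresponds to a slope of 0.37/1.596 = 0.232 SD of adherence per SD of score. If 0.37 is in within-half SD units:

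- residual variance = 1 − 0.232² × (1 − 1.596²/4) = 0.980
- correlation = 0.232/√(0.232² + 0.980) = 0.228
- Fisher z power = Φ(atanh(0.228) × √237 − 1.960) = Φ(3.573 − 1.960) = 94.7%

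If 0.37 is in total SD units, the result is 95.3%. Simulation (20,000 runs) gave 94.6% for the full score and 81.4% for the split. The full score would reach 80% power with (2.802/atanh(0.228))² + 3 ≈ 149 patients instead of 240.

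**3. Dependence on the score's shape.** The split retains a share of the information equal to (gap/2)², where gap is the separation in score SDs.

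| Score shape | Gap | Share retained | Full-score power, n = 240 |
|---|---|---|---|
| Normal | 1.596 | 0.64 | 94.7–95.3% |
| Uniform | 1.732 | 0.75 | 91–92% |
| Exponential | 1.386 | 0.48 | 98.5–98.8% |
| Simulated four-item | – | – | 92–95% (split 80–82%) |

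**4. A test of moderation proper.** Compare the intervention effect between high and low scorers across both arms of the 480. The protocol gives no target for this, so 0.37 SD is carried over as an assumption.

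- Split, equal halves: standard error √(4/120) = 0.1826; 0.37/0.1826 − 1.960 = 0.067; power 53%. Unequal halves lower this; over the shapes tried it was about 47–53%.
- Full score, normal: standard error of the slope difference √(2/240) = 0.0913; 0.232/0.0913 − 1.960 = 0.580; power 72%.
- Full score, uniform: slope 0.37/1.732 = 0.2136; 0.2136/0.0913 − 1.960 = 0.380; power 65%.
- Full score, simulated four-item scores: up to 76%, with 36% of patients at the minimum. The exponential shape lies outside this range: 0.267/0.0913 − 1.960 = 0.964, or 83%.

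For a normal score, the difference in effect detectable with 80% power is 2.802 × 0.1826 = 0.51 SD with the split and 2.802 × 0.0913 × 1.596 = 0.41 SD with the full score.

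**5. When linearity fails.** If the truth is a step exactly at the median, the split wins in the one-arm contrast: 81% against 58–63%. With simulated scores where 43% of patients sit at the minimum and the effect plateaus after four score points, it is 80% split against 76% full score. If it plateaus after two points, it is 80% against 63%. With a square-root shape, the full score gains only about 6 points.

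**The case against.** The split appears only where the sample size is derived. The analysis text leaves the coding open, although it does name a cut when one is intended, as for self-reported adherence; and model coding is often left to a statistical analysis plan, which is not at hand. This stands in part. The protocol does not lock the split into the model, but it does call the high/low comparison the main moderation contrast, and it states no other coding.

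A reader might infer that the split lowers the power of the moderation test from about 95% to about 80%. The documents do not support that. The 95% is the power to detect an association between score and adherence among treated African American patients. It is not the power of an arm-by-score test, where keeping the full score moves power at 0.37 SD from about 47–53% to about 65–76%, still below 80%. The restriction to one arm is a separate matter that this change does not cure.

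A reader might also infer that the full score is better whatever the truth. That does not follow either: the protocol gives neither the score's distribution nor the shape of the relationship, and a heavy floor combined with an early plateau reverses the ranking.

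Finally, the Background describes past discrimination as a moderator to be explored. The primary outcome, H1, H3 and the total of 1,130 are unaffected. This stands, and it limits the weight of the point.

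**Conclusion.** The point holds as an inefficient choice, not as an error: the stated power is correct. If the relationship is roughly linear, the median split discards about a third of the information for a normal score (a quarter for a uniform score, about half for an exponential one). The cost is roughly 9 to 17 percentage points in the protocol's one-arm contrast and about 20 points in an arm-by-score test. These sizes rest on assumed score shapes and on linearity. The direction held for every score shape tried under a linear relation, but not when a heavy floor met an early plateau. The protocol gives no reason to expect a step at the median, and readability does not require cutting the score before testing. This is a cheap improvement that bears on H2 only.

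**What to change.** In Sample size estimation and in Statistical Analysis, state that the prior-discrimination score enters the mixed model as a continuous moderator, and make the test on the score the main moderation test. Restate the detectable effect for that test. For readability, report model-estimated effects at prespecified raw score values; sample percentiles would depend on this sample just as the median does. Keep the high/low split as a descriptive or sensitivity analysis, and add a check for non-linearity, such as a quadratic term.

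The cost is a few sentences and one power calculation, with no new data or patients. The downside is reliance on approximate linearity, which the non-linearity check and the retained split would help to expose.
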